## Abstract

**Background:**

In case of locally advanced and/or non-metastatic unresectable esophageal cancer, definitive chemoradiotherapy (CRT) delivering 50 Gy in 25 daily fractions in combination with platinum-based regimen remains the standard of care resulting in a 2-year disease-free survival of 25% which deserves to be associated with new systemic strategies. In recent years, several immune checkpoint inhibitors (anti-PD1/anti-PD-L1, anti-Program-Death 1/anti-Program-Death ligand 1) have been approved for the treatment of various solid malignancies including metastatic esophageal cancer. As such, we hypothesized that the addition of an anti-PD-L1 to CRT would provide clinical benefit for patients with locally advanced oesophageal cancer. To assess the efficacy of the anti-PD-L1 durvalumab in combination with CRT and then as maintenance therapy we designed the randomized phase II ARION (Association of Radiochemotherapy with Immunotherapy in unresectable Oesophageal carciNoma- UCGI 33/PRODIGE 67).

**Methods:**

ARION is a multicenter, open-label, randomized, comparative phase II trial. Patients are randomly assigned in a 1:1 ratio in each arm with a stratification according to tumor stage, histology and centre. Experimental arm relies on CRT with 50 Gy in 25 daily fractions in combination with FOLFOX regimen administrated during and after radiotherapy every two weeks for a total of 6 cycles and durvalumab starting with CRT for a total of 12 infusions. Standard arm is CRT alone. Use of Intensity Modulated radiotherapy is mandatory.

The primary endpoint is to increase progression-free survival at 12 months from 50 to 68% (HR = 0.55) (power 90%; one-sided alpha-risk, 10%). Progression will be defined with central external review of imaging.

**Ancillary studies are planned:**

PD-L1 Combined Positivity Score on carcinoma cells and stromal immune cells of diagnostic biopsy specimen will be correlated to disease free survival. The study of gut microbiota will aim to determine if baseline intestinal bacteria correlates with tumor response. Proteomic analysis on blood samples will compare long-term responder after CRT with durvalumab to non-responder to identify biomarkers.

**Conclusion:**

Results of the present study will be of great importance to evaluate the impact of immunotherapy in combination with CRT and decipher immune response in this unmet need clinical situation.

**Trial registration:**

ClinicalTrials.gov, NCT: 03777813.Trial registration date: 5^th^ December 2018.

## Background

Esophageal cancer is the 6^th^leading cause of cancer death worldwide with two main histologic subtypes squamous cell carcinoma and adenocarcinoma. Its incidence in France is higher than in any other European country with 5500 new cases in 2018 and carries a dismal prognosis [1].

In case of locally advanced disease and/or non-metastatic unresectable disease, definitive chemoradiotherapy (CRT) delivering 50 Gy in 25 daily fractions in combination with FOLFOX (a combination of oxaliplatin, 5-fluoro-uracil, and acid folinic) administrated during and after radiotherapy every two weeks for a total of 6 cycles is a standard therapeutic option resulting in a 2-year disease-free survival (DFS) of 25% [2]. The majority of patients still die from metastatic progression and the overall benefit of improved local control with optimal CRT remains to be associated with new systemic strategies to prevent metastatic progression.

In recent years, several immune checkpoint inhibitors have been granted approval by agencies such as the US Food Drug Administration (FDA) and the European Medicine Agency (EMA) for the treatment of various solid malignancies including metastatic melanoma, non-small-cell lung carcinoma and esophageal cancer [3, 4]. Last year, anti-Program-Death 1 (anti-PD-1) pembrolizumab has been granted approval by FDA and EMA in first-line of esophageal metastatic disease in combination with platin-based chemotherapy with a PD-L1 combined positive score (CPS) ≥ 10 [5]. Recently in a randomized phase III study (Checkmate 577), the addition of nivolumab for up to one year in the adjuvant setting of resectable esophageal carcinoma with incomplete response after neo-adjuvant CRT resulted in improved median PFS from 11.0 to 22.4 months with a manageable safety profile [6]. In locally advanced esophageal cancer patients PD-L1 expression is correlated with poorer overall survival and its expression in tumor cells increased in esophageal cancer patients after neoadjuvant CRT hence supporting the rationale of PD-L1 blockade in combination with CRT [7].

It is now established that efficacy of chemotherapy and radiotherapy partly relies on the immune system [8]. Combination of immune checkpoint inhibitors and radiation therapy (RT) represents a promising therapeutic strategy supported by a strong pre-clinical rationale [9]. Beyond its local effect, RT induces a rare systemic antitumor response mediated by immune recognition of antigen released from the irradiated tumor known as abscopal effect [10]. Although the primary goal of RT is to achieve local tumor control, ionizing radiations (IR) enhance tumor antigen release that activates immune recognition [11].

The biological mechanisms of the phenomenon called abscopal effect rely on RT to elicit immune tumor recognition that is mediated by various biological mechanisms: recruitment of tumor infiltrating lymphocytes, MHC class 1 antigen presentation in tumor cells that may induced enhancement of tumor antigen presentation or uptake by dendritic cells, cytokines release that facilitates the recruitment of T cells to tumor [12]. PD-1 receptor or its ligand is strongly expressed either on activated T-cells, antigen presenting cells or tumor cells. The activation of these endogenous immune check points play a crucial role to actively evade cytotoxic T-cell activation and immune mediated tumor destruction. The negative regulation of T cells immune response mediated by the PDL-1/ PD-1 axis or the depletion of T cells is known to abrogate RT efficacy [13].

In a randomized phase III study (PACIFIC trial) the addition of anti-Program-Death Ligand 1 (anti-PD-L1) durvalumab for up to 12 months or placebo after definitive radiotherapy up to 66 Gy and platinum-based chemotherapy in unresectable locally advanced non-small cell lung carcinoma showed an increase of median progression-free survival from 5.6 months to 16.8 months and an increase of estimated 5-year rates for OS for durvalumab and placebo were 42.9% versus 33.4% respectively [14].

As such, we hypothesized that the addition of an anti-PD-L1 to CRT would provide clinical benefit for patients with locally advanced oesophageal cancer in increasing local response and preventing metastatic progression. To assess the efficacy of anti-PD-L1 durvalumab in combination with CRT and then as maintenance therapy we designed a randomized 1:1 phase II trial, ARION (Association of Radiochemotherapy with Immunotherapy in unresectable Oesophageal carciNoma ARION UCGI 33/PRODIGE 67). This ongoing prospective intergroup PRODIGE (*Partenariat de Recherche en Oncologie DIGEstive*) open labelled study is supported by Astra Zeneca and sponsored by UNICANCER [15].

## Methods and design

ARION UCGI 33/PRODIGE 67 study is approved by the UNICANCER Gastro-Intestinal Group (UCGI) and by INCa-Labeled cooperative intergroup PRODIGE. It is a French national trial, multicentric, randomized and comparative phase II evaluating the efficacy of durvalumab combined with chemoradiotherapy compared to the standard CRT. The study is conducted in strict compliance with the protocol. Changes will be included in an amended version of the study protocol. Amended trial protocols with substantial modifications are submitted to the ANSM and to the CPP by the sponsor, according to the French regulation.

The Sponsor is responsible to notify to all investigational centers any amendment approved by the French authorities.

### Study objectives

The primary objective is to assess the efficacy of durvalumab, initially delivered in combination with FOLFOX and IMRT 50 Gy and then as maintenance therapy for treating patients with locally advanced esophageal cancer (adenocarcinoma or squamous cell carcinoma), in terms of centrally reviewed PFS (cPFS). As it is not a placebo-controlled study, an external anonymized blinded independent central review (BICR) of CT-scans (Response Evaluation Criteria in Solid Tumours RECIST v1.1) at baseline, M6, M9, M12, M18, and M24 is planned (see Fig. 1). Secondary objectives are PFS, overall survival, tolerance of the study treatments and quality of life.

**Fig. 1 Fig1:**
[figure not shown]
Study design

Patients fulfilling the inclusion criteria are randomized between the two arms according to a 1:1 ratio using minimization method according to the following factors: *tumor stage, histology and center*.

➢ Arm A = experimental arm: durvalumab in combination with FOLFOX and definitive IMRT.Chemoradiotherapy (CRT): IMRT 50 Gy in 25 daily fractions in combination with FOLFOX regimen administrated during and after radiotherapy every two weeks for a total of 6 cycles. Durvalumab: 1500 mg one infusion q4w starting with CRT for a total of 12 cycles.➢ Arm B = standard arm: CRT: FOLFOX and definitive IMRT.Chemoradiotherapy IMRT 50 Gy in 25 daily fractions in combination with FOLFOX regimen administrated during and after radiotherapy every two weeks for a total of 6 cycles.

Given the lack of safety data from this association, a safety run-in of the 6 first patients was planned to assess for the absence of dose limiting toxicity (DLT).

### Sample size and main statistical analysis

The main objective is to increase 12-months centralized progression-free survival (cPFS) from 50 to 68%. This corresponds to a hazard ratio of 0.55. A total of 74 events expected are necessary for 90% power to detect this difference if it is true using a one-sided logrank test at the 10% level of significance and a 1:1 randomization (arm A: arm B). Target difference, type I and II error rates are compatible with recommendations performed by Rubinstein for comparative phase II trial [16].

Primary endpoint will be analyzed on the Intent-to-Treat (ITT) population when the required number of events is reached. The Kaplan–Meier approach will be used to estimate cPFS rates for each treatment arm. The primary endpoint analysis will be evaluated using a Cox regression analysis with 90% confidence interval (one-sided).

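### The primary Cox comparison names none of the minimisation factors; run as worded it would be valid but mildly conservative, giving up about 1 to 3 points of power if stage and histology are modestly to moderately prognostic

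*Protocol article*

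**What the plan says.** **Allocation.** The abstract describes 1:1 assignment "with a stratification according to tumor stage, histology and centre". The legend to Fig. 1 says that this is done "using minimization method according to the following factors: *tumor stage, histology and center".

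**Sizing.** Under Sample size and main statistical analysis, the aim is to "increase 12-months centralized progression-free survival (cPFS) from 50 to 68" per cent. The article adds: "This corresponds to a hazard ratio of 0.55". It then says: "A total of 74 events expected are necessary for 90% power to detect this difference", "using a one-sided logrank test at the 10% level of significance and a 1:1 randomization".

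**Analysis.** The same section sets the ITT population, the timing (when the required events are reached), Kaplan–Meier estimates by arm, and then: "The primary endpoint analysis will be evaluated using a Cox regression analysis with 90% confidence interval (one-sided").

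Stage, histology and centre appear in the allocation text only. Neither the sizing sentence nor the analysis sentence mentions them, and neither says unadjusted or unstratified.

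**The concern.** Minimisation makes the arms more alike on the chosen factors than simple randomisation would. If those factors predict progression and the model leaves them out, two things follow. The usual standard error does not credit the forced balance, so the test rejects less often than its nominal 10% under the null. And the hazard ratio from a treatment-only Cox model lies closer to 1 than the ratio within stage and histology groups. Both cost power.

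The trial is small (120 patients planned, 74 events), and the factors are known for every patient at randomisation. The analysis section is otherwise specific about population, timing, model, sidedness and interval, so a reader who follows it literally would fit treatment alone.

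**Working it through.** **1. The plan's own figure.** The inputs are hazard ratio 0.55, one-sided 10%, power 90% and 1:1 allocation. By Schoenfeld's formula:

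events = 4 × (1.2816 + 1.2816)² / (ln 0.55)² = 26.28 / 0.3574 = 73.5, rounded up to **74**.

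This reproduces exactly. Power at 74 events is Φ(√74/2 × 0.5978 − 1.2816) = Φ(1.290) = 0.901. The unrounded ratio from the stated rates is ln 0.68 / ln 0.50 = 0.556, which gives 77 events, or power 0.893 at 74. The formula needs no strata, so the log-rank wording in the sizing sentence is not faulty.

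**2. Power with and without the factors.** Simulation with 120 patients, minimisation with an assumed probability of 0.8, analysis at the 74th event, and true hazard ratio 0.55 within stage and histology groups; 3,000 trials per row. The prognostic hazard ratios are assumptions.

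| Prognostic HR, stage / histology | Plain log-rank | Cox score test adjusted for stage and histology | Gain (points) |
|---|---|---|---|
| none | 0.899 | 0.900 | 0.1 |
| 1.5 / 1.3 | 0.886 | 0.900 | 1.4 |
| 2.0 / 1.5 | 0.871 | 0.896 | 2.5 |
| 2.5 / 1.5 | 0.851 | 0.894 | 4.3 |

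The type I error of the adjusted score test was about 10 to 11%. Monte Carlo error is about √(0.9 × 0.1 / 3,000) = 0.5 points.

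**3. Type I error and estimate.** A separate set of 6,000 trials per setting assumed stage split 50/50, histology 65/35, 18 centres without prognostic effect, and uniform accrual over 42 months.

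| Prognostic HR | Plain: one-sided type I error | Plain: average HR | Plain: power | Stratified log-rank: power |
|---|---|---|---|---|
| none | 10.2% | 0.55 | 0.89 | 0.88 |
| 1.5 / 1.3 | 9.6–9.8% | 0.556–0.558 | 0.89 | 0.88 |
| 2.0 / 1.5 | 8.9–9.2% | 0.570–0.573 | 0.87 | 0.88 |
| 3.0 / 2.0 | 7.6–8.3% | 0.601–0.603 | 0.83 | 0.88 |

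In the same runs the covariate-adjusted Cox model (Wald test) had type I error 10.1–10.6%, average hazard ratio 0.54–0.55 and power 0.89–0.90 throughout.

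**4. How much of the gain is extra type I error?** At 74 events and hazard ratio 0.55 the expected statistic is √74/2 × 0.5978 = 2.571. A test running at 10.6% has critical value 1.248, so power is Φ(2.571 − 1.248) = 0.907 against 0.901 at exactly 10%. About 0.6 points of the gain could come from this.

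**5. With the arm-level rates held at 50% and 68%.** The stated target is a difference between arms as a whole. With those rates fixed (3,000 trials per setting), plain log-rank power was 0.887, 0.878 and 0.878 at prognostic ratios 1.5/1.3, 2.0/1.5 and 2.5/1.5. The analytic value is 0.893, so the largest shortfall is 0.893 − 0.878 = 1.5 points. Adjusted Cox gave 0.898 to 0.912, again a gain of about 1 to 3 points.

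**The case against.** The strongest objection is that the article is silent, not wrong. Cox regression can carry covariates or strata, and a journal article commonly leaves the list to the full protocol or SAP. A reader might infer that the plan prescribes an unadjusted model; the text does not say so. That stands, and it makes the point conditional. The point survives because the analysis is otherwise specified in detail, and because there is a better method to recommend, not only a gap to fill.

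A reader might also infer that the trial is materially underpowered. The documents do not support this. They give no prognostic effect for stage or histology, and with the target read as arm-level rates the plain test stays within about 1.5 points of its analytic power.

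A third tempting reading is that an unadjusted hazard ratio of about 0.57 would be a biased estimate. It is mostly a different quantity. The plan's target is marginal (0.556 from the stated rates), and the treatment-only model estimates a marginal contrast. The 0.55 in steps 2 and 3 is conditional on stage and histology, so part of the loss seen there follows from that choice.

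Finally, the departure is conservative. Without adjustment the false-positive rate falls and does not rise.

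**Conclusion.** The point holds as a modest improvement, conditional on two things the article does not settle: that the primary model really omits stage and histology, and that they are prognostic. If both are true, the plain comparison is valid, slightly conservative, and gives up about 1 to 3 points of power for modest to moderate prognostic effects. The loss is about 4 points at 2.5/1.5, and nil if the factors are not prognostic. The 74-event calculation needs no change.

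These sizes rest on assumed prognostic hazard ratios, a minimisation probability of 0.8 and exponential times, none of which the documents give.

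**What to change.** Check the full protocol and SAP. If they already include stage and histology in the primary model, nothing needs to change. If not, amend the analysis before the 74-event cut, without sight of outcome by arm:

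- Base the primary decision on the one-sided 10% score test for treatment in a Cox model with tumour stage and histology as covariates, in the ITT population.
- Report the hazard ratio and its one-sided 90% bound from that same model.
- Leave centre out: 120 / 18 is about 7 patients per centre and 74 / 18 about 4 events.
- Keep the unadjusted log-rank and Cox results as a sensitivity analysis, with the Kaplan–Meier estimates by arm.

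A log-rank stratified by stage and histology should not be the lead option. Its power stayed at 0.88 in every setting, and it can lose 1 to 2 points against the plain test when the factors are weak.

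**Cost.** One sentence in the plan and no new data; the event target stays at 74. There are two downsides to accept openly. The type I error may sit slightly above nominal (about 10 to 11% in simulation). The adjusted hazard ratio is conditional, so it should be read beside the marginal 50% and 68% target and not as a direct estimate of it.

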### Patient selection

Inclusion and exclusion criteria are listed in Table 1 (Last version Protocol v5.0_13 Dec 2021).

**Table 1 Tab1:** List of eligibility criteria of the ARION study

Main inclusion criteria	Main exclusion criteria
• Histologically proven squamous cell carcinoma or adenocarcinoma of the esophagus, • Unresectable disease due to anatomical consideration or medical condition (patient unfit for surgical procedure) according to local multidisciplinary team meeting, • Presence of at least one measurable lesion > 10 mm with spiral CT-scan, • No prior therapy for the esophageal cancer including chemotherapy or radiotherapy prior to the study, except anterior out of field radiotherapy, received for treatment of another primary tumor considered in remission, in the past 5 years, • Age ≥ 18 years old, • WHO performance status < 2, • Body weight > 35 kg, • Patients must have provided consent for the study by signing and dating a written informed consent form prior to any study specific procedures, sampling, or analyses, • Patient must be affiliated to a social security regimen	• Previous treatment with an PD-1, PD-L1 or CTLA-4 inhibitor • Metastatic disease, • Patients should not receive live vaccine 30 days prior to study treatment • Female patients who are pregnant or breastfeeding • Uncontrolled intercurrent illness including, but not limited to diabetes, hypertension, pulmonary failure, chronic renal or hepatic diseases, active peptic ulcer disease or gastritis, active bleeding, diatheses (non-exhaustive list), • Clinically significant cardiac disease or impaired cardiac function, • Current or prior use of immunosuppressive medication within 28 days before the first administration of durvalumab (exception: systemic corticosteroids at physiologic doses not exceeding 10 mg/day of prednisone or equivalent are allowed as well as steroids as premedication for hypersensitivity reactions (e.g., CT scan premedication)—Topical, inhaled, nasal, and ophthalmic steroids are allowed, • Active or prior documented autoimmune or inflammatory disorders • Known primary immunodeficiency or active HIV, • Patient with a dihydropyrimidine dehydrogenase (DPD) deficiency (the test must be done for all patients before 5-FU administration), • Known active or chronic viral hepatitis or history of any type of hepatitis within the last 6 months indicated by positive HBs antibody test for hepatitis B or hepatitis C virus ribonucleic acid (HCV antibody), • Current pneumonitis or interstitial lung disease, • Other invasive malignancy within 2 years prior to entry into the study, except for those treated with curative surgical therapy alone, • History of severe allergic reactions or hypersensitivity to any unknown allergens or any components of the study drug, • Any prior corticosteroid-refractory immune-related adverse event (irAE), • Oeso-tracheal or oeso-bronchial fistulae, • Major surgery within 28 days prior to the first dose of study treatment

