The monitors and CRAs in charge of trial monitoring will be mandated by the sponsor. They must have access to all patient data as necessary for their duty in accordance with the national regulatory requirements. The monitors and CRAs are bound by professional secrecy under the national regulatory requirements. Written reports must be issued to ensure monitoring visit traceability. In order to ensure the optimal research quality control, the investigator commits to provide the monitor with direct access to all patient files.

Continuous variables will be summarized by arm, using median, minimum, maximum and number of available observations. Qualitative variables will be summarized by arm using: counts, percents, number of missing data. Primary endpoint will be analyzed on the ITT population when the required number of events has been reached.

All randomized patients signed a written informed consent form. Patient information and informed consent from the patient must be handled in accordance with the “French regulation, especially article L.1122–1 and subsequent articles.

The first patient was enrolled in May 2019 and eighteen centers from the PRODIGE Group are participating. To date, 86 out of 120 patients are already enrolled.

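### Minor: the hepatitis exclusion in Table 1 misnames its markers, giving HBs antibody as the sign of hepatitis B and labelling hepatitis C RNA as an antibody test

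*Protocol article*

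**What the plan says.** The line is one of the main exclusion criteria in Table 1 (Protocol article, Patient selection). It opens with the condition to be excluded: "Known active or chronic viral hepatitis or history of any type of hepatitis within the last 6 months". It then says how that condition is recognised: "indicated by positive HBs antibody test for hepatitis B or hepatitis C virus ribonucleic acid (HCV antibody", where the bracket closes and the criterion ends.

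The table is offered as current text: "Inclusion and exclusion criteria are listed in Table 1 (Last version Protocol v5.0_13 Dec 2021". No other part of the article defines or corrects these tests. The only other liver wording is the mention of chronic hepatic disease under uncontrolled illness in the same table, and it names no serology.

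**The concern.** An exclusion criterion should name a test that identifies the patients it means to exclude. Here the hepatitis B marker is a sign of immunity, and the hepatitis C marker is two assays presented as one.

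Two things are at stake, both modest. First, someone applying the line word for word could turn away a patient who was vaccinated against hepatitis B or recovered from it long ago. Second, for a patient who has cleared hepatitis C (antibody-positive, RNA-negative), the line gives no single answer. The RNA reading leaves that patient eligible and the antibody reading excludes the same patient. With "eighteen centers from the PRODIGE Group are participating" (Data management), two centres could answer differently if their protocol has this wording.

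**Working it through.** There is no stated figure to reproduce, and no calculation of power, events or sample size is involved. The check compares what the criterion means to exclude with what each named test shows.

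**Inputs.** The condition and the named markers come from Table 1. The meaning of the tests is basic serology:
- HBs antigen: current infection.
- HBs antibody: vaccination or past infection.
- HCV RNA: current viraemia.
- HCV antibody: exposure, past or present.

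**Hepatitis B.** The table names the antibody ("indicated by positive HBs antibody test for hepatitis B").

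| HBs antigen | HBs antibody | Flagged by named marker | Currently infected | Agreement |
|---|---|---|---|---|
| − | − | no | no | yes |
| − | + | yes | no | **no** |
| + | − | no | yes | **no** |
| + | + | yes | yes | yes |

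The named marker disagrees with infection status in 2 of 4 profiles. The opening words already exclude anyone with known infection, which removes the antigen-positive, antibody-negative profile where the infection is known. That leaves 2 − 1 = 1 profile: antigen-negative, antibody-positive. Within it, a patient who had hepatitis in the last 6 months is properly excluded by the history clause. The patients affected are those vaccinated, or recovered more than 6 months ago.

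**Hepatitis C.** The table names RNA and puts the antibody in brackets.

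| HCV antibody | HCV RNA | Excluded on RNA reading | Excluded on antibody reading | Agreement |
|---|---|---|---|---|
| − | − | no | no | yes |
| + | − | no | yes | **no** |
| − | + | yes | no | **no** |
| + | + | yes | yes | yes |

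The two tests disagree in 2 of 4 profiles. Known viraemia is excluded by the opening words, which again leaves 2 − 1 = 1: antibody-positive, RNA-negative.

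These counts show where the wording fails. They do not measure size, because a profile may hold many patients or none, and the article gives no marker data.

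**Does the grammar rescue the line?** The serology phrase can be attached in two ways. If it governs the whole criterion, HBs antibody is the wrong marker of active or chronic disease. If it governs only the 6-month history, the antibody cannot tell recent infection from old infection or from vaccination. The hepatitis C wording is inconsistent on both readings.

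**Patients who could still be affected.** Data management reports 86 of 120 patients enrolled when the article was written. A later correction could therefore bear on at most 120 − 86 = 34 inclusions. This is an upper limit on those still to be screened against the rule and enrolled, not an estimate of patients misclassified.

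**The case against.** The strongest reply is that the criterion excludes a condition and offers serology only as evidence of it. A vaccinated patient has no active, chronic or recent hepatitis, and a patient who recovered years ago is outside the 6-month window. On that view, refusing either means ignoring the words that define the exclusion, and most investigators would infer the intended tests. This largely stands: wrongful exclusion is a possible literal reading, not the natural one. It does not make HBs antibody a suitable indicator, and it does not settle which hepatitis C test is meant.

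A second reply is that centres work from the full protocol, not from the article: "The study is conducted in strict compliance with the protocol" (Methods and design). Version 5.0 is not shown, and the table lists only main criteria, so the slip may exist only in the article. This also stands, and it is why the first step is to look at v5.0. It does not excuse the table, which makes a positive statement and makes it wrongly; this is not detail left to the full protocol.

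Two stronger readings may tempt a reader, and the document supports neither.
- **Undetected carriers.** One might infer that the line lets in antigen-positive, antibody-negative carriers. Known infection is excluded by the opening words. For unknown infection, the line as shown orders no screening, unlike the DPD line in the same table, where "the test must be done for all patients before 5-FU administration". Nothing can be concluded about undiagnosed carriers.
- **Bias.** One might infer an effect on the comparison of arms. Eligibility is decided before allocation: "Patients fulfilling the inclusion criteria are randomized between the two arms according to a 1:1 ratio" (Study design, Fig. 1). An error in this line acts on both arms alike and does not touch the primary analysis.

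**Conclusion.** The line is wrong as written, at the lowest level of severity. It names an immunity marker as the sign of hepatitis B and treats two different hepatitis C tests as one. The conclusion rests on the plain text of Table 1 and the basic meaning of four laboratory tests; no prevalence or outside figure is assumed.

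Its practical reach is limited to two kinds of patient: those immune to hepatitis B, who could be excluded on a literal reading, and those antibody-positive but RNA-negative for hepatitis C, whose status is undefined. There is no evidence that any patient was wrongly excluded or that centres differed. No effect on safety, randomisation, sample size or the primary analysis is claimed. Whether the error ever operated depends on the wording of v5.0.

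**What to change.** Check the criterion in protocol v5.0. Then name positive HBs antigen as the hepatitis B marker and positive HCV RNA as the hepatitis C marker, and delete the bracketed antibody. An antibody-positive, RNA-negative patient is then clearly eligible unless the 6-month history clause applies.

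- **If only the article is wrong:** correct one line of Table 1. Nothing changes for the centres.
- **If v5.0 has the same wording:** the cost is more than a memo. Methods and design says that changes go into an amended protocol version, that substantial modifications are submitted to the ANSM and the CPP, and that the sponsor notifies the centres of approved amendments. The article does not show whether this change would count as substantial. The economical course is to include it in the next amended version and notify the eighteen centres. It would apply only to patients not yet enrolled.
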